### Outcomes

#### Primary Outcome

The primary outcome is the change in NIHSS score at 48 weeks [21]. This scale evaluates levels of consciousness, command compliance, eye movement, visual field defects, facial paralysis, limb motor dysfunction, ataxia, speech expression, and other parameters.

#### Secondary Outcomes

The 3 secondary outcomes are the change in TCM syndrome scores, cerebral infarction recurrence rates, and the change in Rankin Scale scores.

A comparison of TCM syndrome scores before and after the medication will be conducted. Based on the guiding principles for clinical research of new Chinese medicines [22], efficacy is categorized as cured, markedly effective, effective, or ineffective according to the change in TCM syndrome scores. TCM symptoms include dizziness, headache, irritability, limb stiffness, neck stiffness, limb numbness, excessive phlegm, shortness of breath, fatigue, spontaneous sweating, dry stool or constipation, dry mouth or thirst, red or dark tongue, and yellow-greasy tongue coating.

In addition, we will use an intelligent TCM diagnostic device (produced by Shenzhen Huiyibida Medical Technology Co, Ltd) to collect tongue images, tongue coating, and pulse information from patients at multiple timepoints. Two study physicians will independently record patients’ clinical symptom information to monitor changes in TCM symptoms and the potential evolution of syndromes.

The cerebral infarction recurrence rate will be evaluated every 12 weeks by CT or MRI and calculated as the number of recurrent cases / the total study population × 100%.

Finally, a comparison of pretreatment and post-treatment Rankin Scale scores will be conducted [23]. The Rankin Scale evaluates neurological recovery after stroke in 6 levels: 0=no symptoms at all, 1=symptoms present but no significant disability, 2=slight disability, 3=moderate disability, 4=moderately severe disability, 5=severe disability, and 6=death.

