**Methods:**

This study adopts a multicenter, randomized controlled clinical trial design. A total of 126 patients aged 30-70 years in the recovery phase of cerebral infarction will be recruited and randomly assigned in a 1:1 ratio to either the study group (n=63, receiving conventional treatment plus Qizhi Jieyu pill) or the control group (n=63, receiving conventional treatment alone). The intervention period will last 12 weeks, and the total follow-up period will be 48 weeks. The primary outcome is the change in the National Institutes of Health Stroke Scale score at week 48. Secondary outcomes include changes in traditional Chinese medicine syndrome scores, the recurrence rate of cerebral infarction, and modified Rankin Scale scores. Adverse events will be recorded and used to assess the safety profile. All data analyses will be performed according to a prespecified statistical analysis plan.

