#### Statistical Analysis Plan

A statistical analysis plan was formulated prior to the start of the study. It will be finalized after discussion among the statisticians, principal investigators, and sponsor before database lock. This plan describes only the standard statistical requirements.

Statistical analysis will be conducted using SAS version 9.4. All hypothesis tests will be 2-sided, with a significance level of α=.05. *P* values less than or equal to .05 will be considered statistically significant.

For continuous variables, mean, SD, minimum, maximum, and median values will be used for descriptive statistics. Independent samples *t* tests (for normally distributed data) or Wilcoxon rank-sum tests (for non-normally distributed data) will be used for hypothesis testing. Normality of continuous variables will be assessed using the Shapiro-Wilk test before choosing appropriate parametric or nonparametric tests.

For categorical variables, frequency and percentages will be used for description. Chi-square tests or Fisher exact tests will be used for hypothesis testing. Ordinal variables will be analyzed using the Wilcoxon rank-sum test.

Logistic regression will be used to control for confounding factors affecting the outcome measures. We will also analyze the association between syndrome evolution patterns and therapeutic efficacy. In parallel, multivariate linear regression will be used to explore the relationship between outcomes and potential confounders, such as baseline NIHSS score, study center, age, and sex. For adverse events potentially associated with animal-derived components—including itching, rash, allergic reactions, and gastrointestinal discomfort—we will conduct attribution analysis and report their incidence separately.

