## Discussion

### Principal Findings

Given the functional impairments and neurological damage caused by cerebral infarction, it remains one of the leading causes of mortality and disability. Qizhi Jieyu pill has been used in clinical practice for over 10 years, with its primary therapeutic advantages including the improvement of clinical symptoms and reduction in the recurrence rate of cerebral infarction. However, due to the lack of standardized clinical research, there is currently no high-quality, evidence-based support for its efficacy and safety, which limits its widespread clinical application. Therefore, conducting this study to evaluate its effectiveness and safety in the recovery phase of cerebral infarction is of significant clinical value.

The upcoming study adopts a multicenter, randomized controlled clinical trial design, with a rigorously calculated sample size. Given the therapeutic advantages of Qizhi Jieyu pill, we primarily include patients in the recovery phase, which is a critical period for exerting its therapeutic effects. For outcome evaluation, we considered the adverse outcomes caused by cerebral infarction, including disability rates. Thus, we selected the change in NIHSS scores as the primary outcome, and changes in TCM syndrome scores, the recurrence rate of cerebral infarction, and Rankin Scale scores as secondary outcomes. Our standardized design facilitates rigorous and normative evidence acquisition. While the NIHSS and Rankin Scale are internationally recognized neurological assessments, TCM syndrome scores reflect TCM’s holistic evaluation of patient recovery. By combining these, we aim to provide a comprehensive understanding of therapeutic efficacy from both biomedical and TCM perspectives.

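### As a change score on a 0 to 6 scale where 6 is death, the Rankin outcome can rank a death as a smaller worsening than a survivor's decline; the baseline-adjusted grade avoids this at little cost

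*Protocol article*

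**What the plan says.** The Secondary Outcomes section of the protocol article gives the operative definition: "The 3 secondary outcomes are the change in TCM syndrome scores, cerebral infarction recurrence rates, and the change in Rankin Scale scores". It later adds that "a comparison of pretreatment and post-treatment Rankin Scale scores will be conducted", without naming a week.

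The same section describes the scale: "The Rankin Scale evaluates neurological recovery after stroke in 6 levels: 0=no symptoms at all". The list ends with "5=severe disability, and 6=death".

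For the test, the Statistical Analysis Plan section says: "Ordinal variables will be analyzed using the Wilcoxon rank-sum test". That test has no baseline term.

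The shorter lists elsewhere do not repeat the word change next to the Rankin item. The abstract has "Secondary outcomes include changes in traditional Chinese medicine syndrome scores, the recurrence rate of cerebral infarction, and modified Rankin Scale scores", and the Discussion (Principal Findings) has "changes in TCM syndrome scores, the recurrence rate of cerebral infarction, and Rankin Scale scores as secondary outcomes".

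Two further facts matter. The Inclusion Criteria set no limit on baseline Rankin grade. Table 1 schedules the scale at baseline and at weeks 12, 24, 36 and 48.

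**The concern.** Rankin grades are ordered categories, and the top one here is death. As a final grade, death is the worst result whatever the starting point. As a change, the score for a death depends on how disabled the patient was at entry: the worse the entry grade, the smaller the recorded worsening. An unadjusted rank-sum test compares patients across different baselines, so it can place a death below a living patient's decline. Subtraction also treats every one-grade step as equal, which an ordinal scale does not promise.

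At stake is the ordering behind the trial's disability comparison, which the Discussion presents as part of the case for long follow-up. It is a secondary outcome, so neither the sample size nor the primary NIHSS test depends on it.

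**Working it through.** **1. Number of grades.** The plan states six levels. Its list is 0, 1, 2, 3, 4, 5, 6, which is seven. Six is reproduced only if death is left out, yet the same sentence assigns death the value 6.

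**2. Change score for a death.** Change = final grade − baseline grade, so a death scores 6 − baseline. A worsening survivor, with both grades within 0 to 5, can worsen by k grades in 6 − k ways: 5 + 4 + 3 + 2 + 1 = 15 possibilities.

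| Baseline of the patient who dies | Change | Survivor declines that are larger | Ties |
|---|---|---|---|
| 5 | +1 | 10 | 5 |
| 4 | +2 | 6 | 4 |
| 3 | +3 | 3 | 3 |
| 2 | +4 | 1 | 2 |
| 1 | +5 | 0 | 1 |
| 0 | +6 | 0 | 0 |

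There are 6 × 15 = 90 combinations. In 20 the death ranks as the smaller worsening, and 15 tie. Example: a death from grade 4 is 6 − 4 = +2; a survivor going from 1 to 4 is +3. On the final grade there are no inversions. At equal baselines there are none on the change scale either, so the problem needs differing baselines and a test that ignores them.

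**3. How many patients.** The documents give no Rankin distribution or death rate, so these inputs are assumptions: 52 evaluable per group (the protocol's figure before dropout), common odds ratio 2.5, baseline grades 1 to 5 at 15/25/30/22/8%, control week-48 grades 0 to 6 at 8/20/25/22/14/6.5/4.5%, and a baseline effect of 0.6, 1.0 or 1.5 log-odds per grade. In 2000 simulated trials per scenario there were about 3.4 deaths per trial, of which 22%, 34% and 49% scored +1. That is 3.4 × 0.22 = 0.7 to 3.4 × 0.49 = 1.7 patients. Deaths ranked as smaller worsenings than survivors in 1.2% to 1.9% of death–survivor pairs and tied in 5% to 6%. Forcing every death to the worst rank moved the power of the rank-sum test on change from 64.8% to 65.1%, 68.8% to 68.6% and 70.2% to 69.9%. It altered significance in about 1% of trials.

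**4. Which analysis.** A second set of 2000 trials per scenario used the same group size, odds ratio, baseline mix and baseline effects, with deaths at 2% to 4.5% of participants:

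| Baseline effect | Rank-sum on change | Rank-sum on week-48 grade | Rank analysis of grade adjusted for baseline |
|---|---|---|---|
| 0.6 | 60.0% | 66.5% | 71.4% |
| 1.0 | 65.2% | 54.6% | 70.2% |
| 1.5 | 67.7% | 41.9% | 67.4% |

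A further set fitted the proportional odds model itself (400 trials per scenario, 52 per group, odds ratio 2.5, assumed distributions). Power was 67% to 70% for change, 40% to 66% for the unadjusted grade and 69% to 76% for the proportional odds model adjusted for baseline, with type I error near 5%. The simulation standard error of one such figure is about √(0.70 × 0.30 / 400) = 2.3 percentage points, so the lower end of the advantage amounts to no material difference.

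**The case against.** The strongest case against has four parts.

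- **A reader might infer that the abstract and the Outcomes section contradict each other, one using a score and the other a change.** The documents do not firmly support this. The abstract, the Discussion and the Figure 1 legend are condensed lists that open with changes, and that word can govern the later items. The Outcomes section is the operative text and is clear that change is meant. What stands is that the wording should be aligned.
- **A reader might infer that on a six-level scale death has no score.** The sentence that miscounts also assigns 6 to death, so this is a counting slip and does not remove deaths from the outcome.
- **The inversion hardly affects the test.** This stands. A death scored +1 still ranks worse than every stable or improving survivor, and the simulations show almost no effect on power.
- **Change can be the better of the two simple definitions, and the choice of model belongs in the analysis plan.** The first half stands: change had more power than the unadjusted grade in two of three scenarios. The second half stands in part. Model detail can wait for an analysis plan that is not shown, but the protocol itself fixes the outcome as a change score and itself names an unadjusted rank test for ordinal variables.

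**Conclusion.** The point holds as a minor to moderate weakness in how a secondary outcome is defined. The arithmetic needs no assumed data: once grade 6 enters a change score, deaths from baseline grades 2 to 5 can rank as smaller worsenings than some survivors' declines. The practical size does rest on assumptions (odds ratio 2.5, the grade distributions, deaths at a few per cent). On these it is about one or two patients per trial and a negligible shift in power. More deaths, or more patients entering at grades 4 and 5, would enlarge it.

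A reader might go further and say that the disability comparison becomes uninterpretable. The figures do not support that. The reason to act is that a better analysis uses data already scheduled, always ranks death worst, and has power equal to or higher than the change score in the scenarios tried. Sample size and the primary analysis are unaffected.

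**What to change.** Define the outcome as the modified Rankin grade at week 48, on the seven listed grades 0 to 6, with 6 assigned to any death before week 48. Compare the arms with a proportional odds model that has baseline grade as a covariate, in place of the change score. Correct the count of levels to seven. Use the same wording in the abstract, the Secondary Outcomes section and the Discussion. Week 48 is proposed here to match the primary outcome's time point, since the Rankin text names no week; the sponsor should confirm it.

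Do not replace change with the unadjusted week-48 grade: in the simulations that lost up to 67.7 − 41.9 = 25.8 percentage points of power.

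The cost is a wording change in the protocol and analysis plan, plus reliance on a proportional odds assumption. No new visits or data are needed, because baseline and week-48 grades are already in Table 1.

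### The TCM secondary outcome is listed as a change in score but also graded into four efficacy categories that are not marked as supportive, so a less informative form could also be tested at .05

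*Protocol article*

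**What the plan says.** The abstract states "Secondary outcomes include changes in traditional Chinese medicine syndrome scores". The Secondary Outcomes section agrees: "The 3 secondary outcomes are the change in TCM syndrome scores, cerebral infarction recurrence rates, and the change in Rankin Scale scores". The Discussion (Principal Findings) also names the change in TCM syndrome scores.

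The Secondary Outcomes section then says "A comparison of TCM syndrome scores before and after the medication will be conducted", and straight after that "efficacy is categorized as cured, markedly effective, effective, or ineffective according to the change in TCM syndrome scores". It refers to a guidance document for the grading and prints no cut-points.

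The Statistical Analysis Plan section gives rules by type of variable and does not name the TCM outcome:

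- Continuous: a t test if normal; otherwise "Wilcoxon rank-sum tests (for non-normally distributed data) will be used for hypothesis testing". The choice rests on a pretest: "Normality of continuous variables will be assessed using the Shapiro-Wilk test before choosing appropriate parametric or nonparametric tests".
- Categorical: "Chi-square tests or Fisher exact tests will be used for hypothesis testing".
- Ordinal: "Ordinal variables will be analyzed using the Wilcoxon rank-sum test".

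All tests are two-sided at .05.

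**The concern.** One outcome appears in two forms. The score change is the listed outcome, but the grades are introduced as the way efficacy is judged, and no sentence makes them descriptive. Each form fits a different rule in the analysis section, so each could yield a P value at .05 for the same underlying data.

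Two things are at stake. First, cutting a score change into four grades treats all changes within a grade as equal, which costs power if the grades are tested. Second, the two forms can disagree on significance. The text does not say which one would carry the conclusion.

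**Working it through.** **Passages side by side.** The abstract, the opening of Secondary Outcomes and the Discussion all name the score change. The grading sentence adds a second form made from that same change. The analysis rules do not choose between them. If the score change fails the normality test, both forms go to a rank-sum test, but on different data: raw changes in one case, heavily tied grades in the other.

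**Inputs for an illustration.** The documents give no SD, effect or grade shares for the TCM score, so a standardized effect has to be borrowed. The Sample Size Calculation section has NIHSS changes of 4.9 and 6, σ = 2.0, α = 0.05 and β = 0.2.

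**The plan's own figure.** n = 2(z₀.₉₇₅ + z₀.₈₀)²σ²/δ² = 2(1.96 + 0.84)² × 4/δ².

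- With δ = 6 − 4.9 = 1.1, n = 51.9, rounded up to 52. This matches the stated 52 per group.
- With the stated difference of 2, n = 15.7, rounded up to 16. This does not match. That discrepancy is a separate matter.

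The effect behind 52 is therefore 1.1/2.0 = 0.55 SD, and it is used here for illustration only.

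**Power on the uncut score.** With 52 per group and 0.55 SD, power is 79.3% by the noncentral t and 80.1% by the normal approximation.

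**Efficiency of the graded rank-sum test.** Let pⱼ be the control-arm grade shares, cⱼ the cut-points on the normal scale, mⱼ the mid-cumulative share of grade j (mean m̄), and dⱼ = φ(cⱼ₋₁) − φ(cⱼ). Relative to the t test on the uncut score, the efficiency is

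e = (Σ mⱼdⱼ)² / Σ pⱼ(mⱼ − m̄)².

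For four equal grades, mⱼ = 0.125, 0.375, 0.625, 0.875 and dⱼ = −0.318, −0.081, 0.081, 0.318. The numerator is 0.2586² = 0.0669 and the denominator is 0.0781, so e = 0.856. Matching 52 per group on the score would take 52/0.856 = 60.7, or 61 per group.

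**Simulation.** 20,000 trials per row, 52 per group, normal change, 0.55 SD shift. Shares are assumed for the control arm and run from lowest to highest grade.

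| Shares (%) | e | n per group to match 52 | t test, score | Rank-sum, grades | Chi-square, grades | t test and graded rank-sum disagree |
|---|---|---|---|---|---|---|
| 25/25/25/25 | 0.856 | 61 | 79.9% | 73.0% | 55.4% | 11.6% |
| 30/40/25/5 | 0.841 | 62 | 79.1% | 73.1% | 56.2% | 10.7% |
| 15/50/30/5 | 0.832 | 63 | 79.3% | 71.8% | 54.2% | 12.1% |
| 20/60/18/2 | 0.796 | 66 | 79.2% | 69.8% | 51.7% | 14.3% |
| 50/35/13/2 | 0.759 | 69 | 79.1% | 70.6% | 52.6% | 13.2% |
| 10/80/9/1 | 0.619 | 84 | 79.8% | 59.6% | 38.9% | 24.7% |

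The rank-sum loss runs from 79.1 − 73.1 = 6.0 points to 79.8 − 59.6 = 20.2 points, the latter when 80% of control participants fall in one grade. The simulation error is about √(0.7 × 0.3/20,000) = 0.3 points.

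**The case against.** The strongest reply is that the endpoint is already named, consistently, in three places, and that no sentence promises a test on the grades. That two P values would be produced is read out of general rules that never mention the TCM outcome. The article also says that its statistical text covers only standard requirements and that the analysis plan will be finalized before database lock, so the choice may be settled there. All of this stands, and it limits the point. What remains is that the article itself presents the grades as an efficacy measure without subordinating them, which is a matter of what is written and not of omitted detail.

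Three stronger readings are tempting, and the documents do not support them.

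- A reader might infer that the sponsor can choose between the two results after seeing the data. The finalization before database lock argues against this. The Randomization section also has outcome assessors blinded, with TCM symptom scores named specifically.
- A reader might infer that participants who enter with few symptoms, whom the inclusion criteria allow, would be graded ineffective although they stay well. The cut-points are not in the documents, so such participants could be graded in any way or treated as not evaluable. A participant who starts at zero shows no improvement on the continuous change either.
- A reader might take the power figures as this trial's expected loss. They borrow the NIHSS effect and assume normality, grade shares and fixed cuts of a raw change. Power is lost only if the grades are what is tested.

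**Conclusion.** The point holds in limited form. The score change is the listed TCM outcome, but the grades derived from it are not marked as supportive, and the analysis rules would allow both to be tested at .05. Testing the grades loses information under every split tried. At an assumed 0.55 SD and 52 per group, power falls from about 79-80% to roughly 60-73% with a rank-sum test, or about 39-56% with chi-square. The t test and the graded rank-sum test disagree on significance in about 11-14% of simulated trials, and in about 25% in the most concentrated case. The direction is firm; the sizes depend on the stated assumptions. The trial is not powered on this secondary outcome, so the consequence is modest, but it can be removed at almost no cost.

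**What to change.** State in the protocol and the analysis plan, before the latter is finalized, that the continuous TCM syndrome score is the single tested TCM secondary endpoint. The sponsor should name one visit for it. The present wording compares scores before and after medication, while Table 1 collects the score at baseline and at weeks 12, 24, 36 and 48. Week 48 is fixed only for the NIHSS outcome.

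Analyse that score by a linear model with treatment arm and baseline TCM score. The baseline is already collected, so this needs no new data. If the variance is equal at both visits and ρ is the correlation between them, the adjusted variance is (1 + ρ)/2 times that of the unadjusted change and so never larger. The article does plan linear regression, but to explore potential confounders, and baseline TCM score is not among the examples it gives.

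Report the cured/markedly effective/effective/ineffective table by arm as description, without a P value. The cost is one or two sentences and the loss of that P value; the table itself stays.

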#### Diagnostic Criteria for Phlegm-Stasis Obstruction Syndrome

The diagnostic criteria are based on the Standards for the TCM Diagnosis and Therapeutic Evaluation of Stroke (Trial Version, 1995), drafted by the Encephalopathy Emergency Research Collaboration Group of the State Administration of Traditional Chinese Medicine [19], and include dizziness and vertigo, profuse and sticky phlegm, dark tongue body, thin white or greasy white tongue coating, and a wiry-slippery pulse.

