#### Inclusion Criteria

Criteria for inclusion in the study are as follows:

Patients diagnosed with cerebral infarction and currently in the recovery phase.Patients aged 30-70 years.Patients who voluntarily signed the informed consent form.

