### Comparison to Prior Work

Compared with prior clinical trials evaluating TCM interventions, such as Tiandan Tongluo capsule [16] and Yindan Xinnaotong soft capsule [15], for poststroke rehabilitation, our study exhibits several innovative features. First, it adopts a longer follow-up period of 48 weeks, enabling a more comprehensive assessment of long-term outcomes such as recurrence and disability. Second, it incorporates a broader inclusion framework without limiting to specific TCM syndrome types, thus improving generalizability. Third, the outcome evaluation uses a dual-system framework that combines biomedical scales (NIHSS and modified Rankin Scale) with standardized TCM syndrome scores, thus enhancing the clinical interpretability of integrative medicine. Finally, our trial is grounded in over a decade of practical experience with Qizhi Jieyu pill and is the first to systematically evaluate this compound through a rigorously designed randomized controlled trial supported by mechanistic insights from pharmacological research.

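### The protocol defines phlegm-stasis obstruction syndrome, but neither entry nor the TCM score follows that definition, so it is unclear what the score and its four efficacy categories refer to

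*Protocol article*

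**What the plan says.** Four places in the protocol article bear on this point.

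- **Participants, under the heading "Diagnostic Criteria for Phlegm-Stasis Obstruction Syndrome".** The features are "dizziness and vertigo, profuse and sticky phlegm, dark tongue body, thin white or greasy white tongue coating, and a wiry-slippery pulse". No other TCM syndrome is given diagnostic criteria.
- **Inclusion Criteria.** The disease requirement is "Patients diagnosed with cerebral infarction and currently in the recovery phase". The other two criteria are age and consent. Neither these nor the Exclusion Criteria mention a TCM syndrome or a minimum TCM score.
- **Secondary Outcomes.** The score is described in two runs: "TCM symptoms include dizziness, headache, irritability, limb stiffness, neck stiffness, limb numbness, excessive phlegm", followed by "shortness of breath, fatigue, spontaneous sweating, dry stool or constipation, dry mouth or thirst, red or dark tongue, and yellow-greasy tongue coating". The tongue signs at issue stand at the close of the second run: "dry mouth or thirst, red or dark tongue, and yellow-greasy tongue coating". The change in score is then graded into four efficacy categories, from cured to ineffective. The same section says that a diagnostic device will also record tongue images, coating and pulse at several time points.
- **Discussion, Comparison to Prior Work.** The authors say of the trial that "it incorporates a broader inclusion framework without limiting to specific TCM syndrome types", and they present this as an aid to generalizability.

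The name of the outcome also varies. It is a syndrome score in the Abstract, Secondary Outcomes and Discussion, but a symptom score in the Figure 1 caption, Table 1 and the Randomization section.

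**The concern.** Diagnostic criteria placed under Participants normally do one of two jobs: they select patients, or they define what the outcome measures. Here they do neither. Entry ignores them, and the score departs from them on one sign and leaves out another. A reader of the final report could not tell whether an improved TCM score means relief of phlegm-stasis obstruction, of some other pattern, or of general post-stroke complaints.

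Two further parts of the article depend on the answer. The Statistical Analysis Plan section intends to relate the way syndromes evolve to efficacy, which requires a statement of what counts as the syndrome. The Discussion presents the standardized TCM score as one of the trial's distinguishing features.

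The four categories raise a related problem. They are built from change in score, in a population with no entry threshold on that score. A participant who starts at or near the bottom of the scale has little or nothing to lose, so the category may reflect the starting point more than the treatment.

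**Working it through.** No sample size, power or alpha figure enters this point, and the plan states no figure to reproduce. The check sets the printed lists side by side.

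**Inputs.** There are five defining features (diagnostic criteria, under Participants) and 14 score items (Secondary Outcomes: seven in the first run quoted, seven in the second).

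| Defining feature | Counterpart among the score items | Result |
|---|---|---|
| Dizziness and vertigo | Dizziness | match |
| Profuse, sticky phlegm | Excessive phlegm | match |
| Dark tongue body | Tongue item, merged with red | match, not specific |
| White coating, thin or greasy | Yellow-greasy coating | conflict |
| Wiry-slippery pulse | None listed | absent |

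**Count by feature:** 3 matched + 1 in conflict + 1 absent = 5.

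**Count by score item:** 3 matched + 1 in conflict = 4, and 14 − 4 = 10 items outside the definition (for example headache, neck stiffness, fatigue and constipation).

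**Entry.** All three inclusion criteria can be met without any of the five features. The Discussion confirms that this is intended. Open entry and a broad score therefore fit each other, and the syndrome criteria are the part without a stated use.

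**Device data.** Coating and pulse are recorded in addition to the score. They do not change the printed item list, but they provide a source from which syndrome status could be derived.

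**Analysis.** For continuous variables the article plans a t test or a Wilcoxon rank-sum test, and for ordinal variables the Wilcoxon test. Its linear regression gives baseline NIHSS, centre, age and sex as examples of covariates. Table 1 shows the TCM score collected at screening/baseline and at all four later visits, so a baseline-adjusted analysis needs no new data.

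**The case against.** The strongest reply is that the outcome is a general one. Secondary Outcomes names no particular syndrome, three other places call it a symptom score, and the Discussion describes it as reflecting a holistic view of recovery. On that reading a broad list suits a broad population, and the only loose end is an unused set of diagnostic criteria. Much of this stands. It is why the point cannot be put as a score that fails to measure the syndrome it names: none is named there, three of the five features are scored, and the wording may leave the item list open. Nor is the open entry an error; it is a stated choice.

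A second reply is that item grading and category cut-offs belong to the cited guidance or the full score sheet, which an article need not reproduce. This also stands. A reader might infer that a patient with a white coating scores nothing on that item throughout, or that a very low starting score turns into a cure. Neither can be shown without the grading rules. The reply does not reach the coating conflict, because the article prints both lists and they differ. An open list would not remove that difference.

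Third, both arms are scored in the same way and outcome assessors are stated to be blinded. No bias between arms follows from the mismatch. What remains is uncertainty about what the outcome means, and possibly some dilution of it.

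Finally, recruitment began in April 2025, so rewriting score items or confining the categories to syndrome-positive participants would redesign the outcome in mid-trial, and the restriction would run against the stated aim of generalizability. That is a fair argument for the lighter remedy.

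**Conclusion.** The point holds as an inconsistency to be reconciled. The article defines phlegm-stasis obstruction syndrome, gives the definition no role at entry, and lists a score that conflicts with it on coating colour and omits the pulse. Which syndrome the score and its four categories refer to, if any, is left unclear, and nothing at entry prevents a participant from starting with little or no score.

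The size is three features matched, one in conflict and one absent, within one secondary outcome. The NIHSS primary outcome and the sample size are untouched. This rests on the item list being substantially as printed. How many participants will lack the syndrome or start with a low score cannot be estimated from the article. A percentage of items that match would be a fault in the score only if phlegm-stasis were its declared target, which the article does not say.

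**What to change.** Keep the broad entry and make three changes.

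1. **Reconcile the diagnostic criteria, Secondary Outcomes and Comparison to Prior Work.** Either state that the outcome is a general post-stroke TCM symptom score that supports no syndrome-specific claim, or state that it targets phlegm-stasis obstruction and resolve the coating and pulse mismatch. Use one name for the outcome throughout.
2. **Record at baseline whether each participant meets the syndrome criteria.** Use the tongue and pulse recordings and the baseline symptom items already collected. This assumes that baseline is one of the device time points, which the article does not say outright.
3. **Make a baseline-adjusted comparison the main analysis of this outcome.** Compare the TCM score between arms by ANCOVA, with baseline score as covariate, in all analysed participants. Present the four efficacy categories descriptively only.

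The cost is some rewording, one derived baseline variable and one covariate. The small downside is that the customary category table becomes supportive. The general-score option leaves the score sheet alone. The phlegm-stasis option costs more, because participants already enrolled were scored on the current items. The article says that the analysis plan is finalized before database lock and that amendments are entered in the trial registry, so the change can be made and dated openly; it should be fixed before any results by arm are seen.
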